### **Data Analysis for the Secondary Endpoints:**

- The prehospital INR delta [between INR- management at the procedure site and INR-on arrival at the hospital] between the two groups will be studied with multilevel logistic regression modeling that will be fitted using a generalized estimating equation method to take into account time and both patient and hospital clustering. Where appropriate, this regression might be adjusted for unbalanced variables.
- The mean difference in fibrinogen levels between the two groups will be compared by a GEE model in the same way as for INR.
- The transfusion requirement will be compared by the number of blood products and plasma units transfused after arrival at the hospital, including packed RBCs, platelet concentrates, fibrinogen, coagulation factors, and Fresh frozen plasma. The transfusion requirement will be assessed at 6 and 24 h, taking the investigating center into account as a stratifying variable.
- The comparison of the median number of RBCs transfused between the two groups will use the Mann–Whitney U test
- The median number of days in the intensive care unit between the two groups will be studied overall and among surviving patients. They will be compared between the two groups by a Mann–Whitney U test.
- For each arm, actuarial survival will be visualized using the Kaplan–Meier estimator and compared with the log-rank test to estimate the effect of FLYP on survival. A multivariable Cox proportional hazard regression model may be fitted in cases of potential imbalance.
- The feasibility of administering FLYP will be judged by the responses to the CRF. page 9
- (Rate of positive responses to the various items)
- Safety outcome: The adverse event incidence will be compared between the two groups, using a Chi2 or a Fisher exact test.
- Exploratory subgroup analysis: we will report the effect size on the INR value in subgroups defined by variables of interest such as the type of injury, the prehospital vasopressor use, the prehospital intubation, the presence of a brain injury.
- Post-hoc analyses to further explain the primary outcome.  
We will measure, with an adapted model, the relationship between the INR value and the ratio of plasma-to-crystalloid volume, which seems to be an indicator of plasma dilution by superadded serum

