## **2.2 Secondary objectives**

- Feasibility of FLYP administration in the prehospital setting
- Show that FLYP improves fibrinogen levels
- To show that the contribution of FLYP decreases the transfusion needs (RBC, plasma, coagulation factors, platelets)
- To show that the contribution of FLYP decreases the length of stay in intensive care
- Compare mortality between the two groups until Day-30

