### **Secondary endpoints:**

- The delta-INR value between the prehospital INR and the INR at hospital arrival. The Point of Care Device Coaguchek® will measure these two INR values
- Listing of technical and logistical difficulties encountered before, during, and after the administration of FLYP.
- The change in fibrinogen level between hospital admission and prehospital setting. The number of RBC units, platelet units, fibrinogen, plasma units, and quantity of coagulation factors administered during the first 24 and 48 hours.
- Length of stay in intensive care
- Length of hospitalization
- 30-days survival.

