#### **7.2.2 What should be declared?**

• **Expected SAEs:**

○ **subject to immediate notification by the investigator:**

- Allergic reactions
- TACO (transfusion-associated circulatory overload)

In sporadic cases, transfusion of fresh frozen plasma may result in allergic reactions or respiratory complications. Therefore, it is important to observe whether the same clinical events occur with FLYP even though the method of manufacturing freeze-dried plasma reduces this risk.

- **not requiring immediate notification by the investigator**

Serious adverse events related to the natural and usual course of the disease and not related to the investigational treatment, nor the acts and procedures added by the research:

- Aggravation of hemorrhagic shock
- Any complications secondary to hemorrhagic shock
- Hospitalization for any length of time: patients suffering from hemorrhagic shock in a traumatic context will benefit from multidisciplinary care in the hospital, including intensive care, surgery, medicine, and functional rehabilitation.
- Death: as the death rate for severe trauma patients is around 50%; given the high activity of the receiving departments, the coordinating investigator must be notified of death via [name] within 72 hours. The coordinating investigator will transmit the information to the promoter (Research and Innovation [REDACTED])

- **Unexpected SAEs:**

Upon **arrival at the hospital**, the patient will be taken care of by the hospital's emergency or intensive care unit, and a follow-up of the initial workup will be performed.

- After the extension workup, a prognosis can be given. Any unexpected worsening of the patient's existing condition that is not consistent with the prognosis given by the initial extension workup should be considered an SAE and reported by the hospital investigating physician.

- **The occurrence of in utero exposure**

Any pregnancy in which the fetus (from pre-embryonic stage to birth) may have been exposed at any time to FLYP, even if not associated with an adverse event, should be reported to the sponsor without delay.

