### **8.2 Anticipated number of people to be included in the research with its statistical justification and anticipated number of people in each research location**

- The recent literature  reports a coagulopathy rate of 50% of severely injured patients on arrival at the hospital.
- We determined that a sample size of 30 patients with coagulopathy in each group was adequate to detect a mean difference of 0.3 in INR values at hospital admission, assuming a standard deviation of 0.4, with a two-sided type I error of 0.05 and a power of 80%.

We chose this 0.3 anticipated effect size pragmatically, based on clinical judgment and the results of one previous observational study  in patients with traumatic hemorrhage of “before-after” FLYP administration

with Prothrombin Time (PT) as the endpoint, showed a significant improvement in PT “after” FLYP. A total of 124 patients were required to observe a statistically significant difference.

Assuming an incidence of coagulopathy of 50%, this resulted in 60 subjects per group. Given the a priori loss of 10% due to lack of informed consent, we rounded the target size of each group to 70 and included a total of 140 patients. To consider a median difference of 0.3 in INR values instead of mean difference, the sample size needs to be approximately 25 coagulopathic patients per group, for a total of 120 patients, based on the same alpha and beta risk assumptions. INR values will be presented according to their median (IQR) and by a three-category variable with cutoff values of 1.2 and 1.5.

[figure not shown]

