## 1711 **16.7 Outcome definitions**

- 1712     ▪ The primary endpoint is the international normalized ratio (INR) at hospital arrival.
- 1713     ▪ Secondary outcomes (prehospital and hospital phases)
- 1714     ▪ The delta-INR value between the prehospital INR and the INR at hospital arrival. The Point of
- 1715     Care Device Coaguchek® will measure these two INR values
- 1716     ▪ The change in fibrinogen between the fibrinogen on hospital admission and the fibrinogen
- 1717     initially collected in the prehospital setting.
- 1718     ▪ Number of RBCs, platelet concentrates, fibrinogen, coagulation factors, plasma, administered in
- 1719     the first 24 and 48 hours.
- 1720     ▪ The total length of stay in intensive care
- 1721     ▪ Survival in the first 30 days.
- 1722     ▪ Collection of technical and logistical difficulties encountered before, during and after the
- 1723     administration of FLYP.

1724

1725

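### Transfusion windows in protocol 8.1 contradict the endpoint, the ICU-stay test scores early death as a short stay, and the documents disagree on whether prehospital FLYP counts as plasma

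*Combined protocol and SAP*

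**What the plan says.** **ICU stay.** The objective in protocol 2.2, repeated in SAP 16.2, is directional: "To show that the contribution of FLYP decreases the length of stay in intensive care". Protocol 8.1 plans: "The median number of days in the intensive care unit between the two groups will be studied overall and among surviving patients", by Mann-Whitney. The SAP's analysis methods for secondary endpoints name a Student or Mann-Whitney test for ICU stay and for hospital days, with no survivor analysis. Neither text gives a rule for patients who die.

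**Mortality.** Protocol 7.2.2 states: "Death: as the death rate for severe trauma patients is around 50" per cent. Section 1.2 gives about 40% when coagulopathy is present. Thirty-day survival is a separate endpoint (Kaplan-Meier, log-rank).

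**Transfusion window.** Section 3.1 counts products "administered during the first 24 and 48 hours", and the summary agrees. SAP 16.7 reads "Number of RBCs, platelet concentrates, fibrinogen, coagulation factors, plasma, administered in" the first 24 and 48 hours. Section 8.1 instead says: "The transfusion requirement will be assessed at 6 and 24 h, taking the investigating center into account as a stratifying variable". The SAP's analysis methods name no window.

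**Plasma count.** Section 8.1 counts units given after hospital arrival, and the summary objective concerns need after admission. Section 3.1 and SAP 16.7 carry no such limit, and the SAP (timing of outcome assessments) starts every calculation at inclusion, which is prehospital. The FLYP arm may receive up to 4 units before arrival (section 3.3.1).

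**The concern.** A patient who dies on day 1 contributes about one ICU day. In a rank or mean comparison of all patients, that is among the best possible results. An arm with more early deaths can then appear to meet the objective of a shorter stay, and an arm that saves lives can appear to lengthen it. Restricting to survivors removes the short stays of the dead, but survival is itself a post-randomisation outcome, so the two survivor groups need not be comparable.

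The other two parts are inconsistencies. As written, 6 h is analysed without being an endpoint and 48 h is an endpoint that section 8.1 does not mention. The plasma total can be read with or without study plasma. Either choice could be settled after the data are seen. Protocol 8.1 and the SAP apply no multiplicity correction, so each secondary test yields its own p-value.

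**Working it through.** **1. The plan's own figure.** The only design calculation is for INR: "a sample size of 30 patients with coagulopathy in each group was adequate to detect a mean difference of 0.3 in INR values", "assuming a standard deviation of 0.4, with a two-sided type I error of 0.05 and a power of 80" per cent.

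- Normal approximation: n = 2 × [0.4 × (1.960 + 0.842) / 0.3]² = 2 × 3.736² = 27.9, so 28 per group.
- t-test: 28.9. Divided by the Mann-Whitney efficiency of 0.955: 30.3. Power at 30 per group is 0.83.
- 30 / 0.5 = 60; 60 / 0.9 = 66.7, so 67, which the plan rounds to 70.

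The stated size reproduces. Nothing below changes it; 70 per arm is used as the trial size. No calculation is given for ICU stay or transfusion.

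**2. Death and ICU stay, first model.** Only the 40 and 50% mortality levels come from the protocol; every other input is assumed. Severity s is standard normal. Stay if alive is exp(ln 8 + 0.6s + 0.5e) days, with e standard normal, capped at 30. Sicker patients die more often. Time to death is exponential, mean 2 days. Red-cell need is Poisson with mean exp(ln 4 + 0.7s), cut short by death within 24 h. FLYP has no effect on underlying stay or red-cell need. There were 1,000 trials of 70 per arm, with Mann-Whitney at two-sided 0.05. The last four columns give the percentage of trials significant in favour of FLYP (nominal 2.5%).

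| Mortality, control / FLYP | Median ICU days, all patients | ICU stay, all | ICU stay, survivors | Red cells at 24 h | ICU stay, death ranked worst |
|---|---|---|---|---|---|
| 50 / 50% | 3.2 / 3.2 | 2.0 | 2.6 | 2.2 | 2.3 |
| 10 / 20% | 6.7 / 5.7 | 24.3 | 6.7 | 4.6 | 0.3 |
| 20 / 30% | 5.7 / 4.7 | 18.0 | 5.7 | 4.4 | 0.4 |
| 40 / 50% | 3.9 / 3.2 | 17.2 | 6.1 | 3.2 | 0.4 |
| 50 / 60% | 3.2 / 2.6 | 16.1 | 5.6 | 3.9 | 0.3 |
| 40 / 60% | 3.9 / 2.6 | 49.8 | 12.3 | 6.5 | 0.0 |

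Simulation error at 17% is √(0.17 × 0.83 / 1000) = 1.2 points, and at 2.5% about 0.5 points. The red-cell rate at 40 / 50% is therefore hardly distinguishable from nominal. At the protocol's mortality levels the false-benefit rate for ICU stay is 16 to 17%; the 24% belongs to lower mortality.

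**3. Second model.** Survivors' stay is lognormal (median 9 days, log-SD 0.8, capped at 30), unrelated to the risk of death; time to death is exponential, mean 1.5 days. All inputs are assumed.

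- Mortality 30% control, 40% FLYP: overall median 5.8 against 4.6 days, and a false significant shortening in about 15 to 16% of trials. Mean ICU-free days fall from 13.0 to about 11.1.
- Mortality 45% control, 30% FLYP: overall median rises from about 4.0 to 5.8 days, and the arm with fewer deaths looks significantly worse in about 28 to 30% of trials. ICU-free days rise from 10.2 to 13.0.
- Survivors only: median 9.0 days in every arm, with two-sided rejection of 4.6 to 4.9%, which is nominal.

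In the first of these cases the loss of ICU-free days is entirely mortality: 13.0 / 0.70 = 18.6 per survivor, and 18.6 × 0.60 = 11.1.

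**4. Windows and plasma, side by side.**

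| Place | Window | Plasma counted |
|---|---|---|
| Summary | 24 and 48 h | Objective: after admission |
| Protocol 3.1 | 24 and 48 h | No limit stated |
| Protocol 8.1 | 6 and 24 h | After hospital arrival; names fresh frozen plasma |
| SAP 16.7, definitions | 24 and 48 h | No limit stated; SAP clock starts at inclusion |
| SAP 16.7, analysis methods | None named | Not specified |

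**The case against.** The strongest reply is that section 8.1 already asks for survivors as well as all patients, and that 30-day survival is tested separately, so a reader would see a mortality difference next to the stay result. Much of this stands. In the second model the survivor comparison shows no distortion at all, and in the first it reaches only about 6 to 7% for a 10-point excess of deaths. But the SAP drops the survivor analysis, the survivor result is unbiased only if death is unrelated to the stay a patient would have had, and the overall test still yields its own p-value on a directional objective.

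A second reply is that ICU-free days largely repeat the survival endpoint. That is fair, as the arithmetic above shows, and is why survivors' stay should remain on view.

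A reader might infer that leaving FLYP out mechanically lowers plasma need in its arm. The documents do not support that. A post-arrival count matches the summary objective, any later saving of plasma is the effect under study, and cumulated plasma volume is described by group elsewhere. What stands is the conflict between definitions.

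A reader might also infer that the 48 h endpoint has no analysis anywhere. The protocol summary and the SAP do name tests for volumes infused or transfused, though without a window, so the gap is in section 8.1.

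**Conclusion.** The point holds in three parts of different strength.

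- **Windows: wrong as written.** Section 8.1 contradicts three other places, and the SAP's analysis methods do not settle it. No assumption is needed.
- **ICU stay: a real weakness of the overall test.** A 10-point excess of deaths gives a false significant decrease in roughly 15 to 24% of trials, against a nominal 2.5%. The direction follows from how stay is scored. The size rests on assumed stay, time-to-death and mortality differences that are not in the documents.
- **Plasma: an unresolved conflict** over whether study plasma counts.

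Two stronger readings are not supported. One is that blood-product counts are distorted as badly as ICU stay: at 24 h the effect appears slight (3 to 5% for a 10-point excess), though it would grow with earlier deaths. The other is that the secondary conclusions would be reversed: that requires reading the overall ICU result without the survivor and mortality results. All of this concerns secondary endpoints; the primary INR comparison and the sample size are untouched.

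**What to change.** 1. In section 8.1, replace 6 and 24 h by 24 and 48 h, name the same windows in the SAP's analysis methods, and label any 6 h result exploratory.
2. In section 8.1 and the SAP, make ICU-free days to day 30, with death counted as 0, the between-arm test, and treat hospital-free days likewise. Use the SAP's modified intention-to-treat population. State how deaths before admission enter, since section 4.3 excludes patients without the arrival sample. Keep ICU stay among survivors as description, restore it to the SAP, and read both beside 30-day mortality.
3. For blood products, show deaths within each window by arm beside the unit counts.
4. Report plasma after arrival and in total including prehospital FLYP. Label the post-arrival count as the test of the summary objective, and state when each clock starts.

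The cost is wording. Discharge dates, dates and times of death, product times and treatment given are already collected (sections 3.3.2 and 3.9). No extra patients are needed. The small downside is that ICU-free days combine mortality with stay, so a difference cannot be read as shorter stay alone.

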### **8.2 Anticipated number of people to be included in the research with its statistical justification and anticipated number of people in each research location**

- The recent literature  reports a coagulopathy rate of 50% of severely injured patients on arrival at the hospital.
- We determined that a sample size of 30 patients with coagulopathy in each group was adequate to detect a mean difference of 0.3 in INR values at hospital admission, assuming a standard deviation of 0.4, with a two-sided type I error of 0.05 and a power of 80%.

We chose this 0.3 anticipated effect size pragmatically, based on clinical judgment and the results of one previous observational study  in patients with traumatic hemorrhage of “before-after” FLYP administration

with Prothrombin Time (PT) as the endpoint, showed a significant improvement in PT “after” FLYP. A total of 124 patients were required to observe a statistically significant difference.

Assuming an incidence of coagulopathy of 50%, this resulted in 60 subjects per group. Given the a priori loss of 10% due to lack of informed consent, we rounded the target size of each group to 70 and included a total of 140 patients. To consider a median difference of 0.3 in INR values instead of mean difference, the sample size needs to be approximately 25 coagulopathic patients per group, for a total of 120 patients, based on the same alpha and beta risk assumptions. INR values will be presented according to their median (IQR) and by a three-category variable with cutoff values of 1.2 and 1.5.

[figure not shown]

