### **1.3 Benefits and potential risks associated with the PREHO PLYO trial**

Bleeding is the leading cause of mortality in severe trauma patients who arrive alive at the hospital. In addition, a specific coagulopathy is found in about 30% of cases in injured patients, civil or war, and is associated with a mortality estimated at 40%.

Recent studies have shown that aggressive and early management of this coagulopathy is associated with an improved vital prognosis.

The use of FLYP allows for the early provision of coagulation factors while respecting the balance between activators and inhibitors and without the risk of increasing coagulopathy by filling with colloids or crystalloids while waiting for the plasmas to thaw.

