### **Data Analysis for Primary Endpoint:**

- For the primary outcome analysis, INR at hospital admission will be considered to have been performed at a comparable time in each patient and will be compared across the two arms with the Mann–Whitney U test. If the initial characteristics of patients are unbalanced between the two groups after randomization, an adjusted analysis will be considered with a regression method.
- When appropriate, both adjusted and unadjusted results will be reported.

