## **8.7 Patients included in the analysis**

Analysis populations will be :

- in intention-to-treat for the safety outcome (ITT: taking into account all randomized patients)
- in modified intention-to-treat analysis for the primary outcome (mITT: taking into account all randomized patients except those for which the eligibility criteria were not met)
- in Per-Protocol (PP: taking into account patients randomized but excluding the patients for which the eligibility criteria were not met and those who were declared free from any haemorrhagia after the hospital check-up.

All statistical analyses will be performed with STATA® software 14.0 or an updated version for Windows (STATA CORP LLC, College Station, Texas, USA).

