## 1620   **16.5   Sample size**

- 1621                   ▪ A previous observational study in a military setting (reference 18 in the study protocol) in
- 1622                   patients with traumatic hemorrhage of "before-after" FLYP administration with Prothrombin
- 1623                   Time (PT) as endpoint showed a significant improvement in PT after FLYP. A total of 124
- 1624                   patients were required to observe a statistically significant difference.
- 1625                   ▪ After the change in the primary endpoint, the sample size was revised and recalculated. Given
- 1626                   that we could not increase the number of patients due to logistical, organizational, and financial
- 1627                   reasons, we calculated the power we could achieve with the same number of patients.
- 1628                   ▪ We calculated that a sample size of 30 patients with coagulopathy would be appropriate in each
- 1629                   group to detect a mean difference of 0.3\* in international normalized ratio values at hospital
- 1630                   admission, assuming a standard deviation of 0.4, with a two-sided type I error of 0.05 and a
- 1631                   power of 80%. Assuming an incidence of coagulopathy of 50% † , this calculation results in 60
- 1632                   patients per group. With an a priori assumed loss of 10% because of lack of informed consent,
- 1633                   we round the size of each group to 70 for a total of 140 patients.
- 1634                   ▪ The concession to the original calculation is essentially a 0.1 increase in the standard deviation
- 1635                   and a power loss from 90% to 80%.
- 1636                   ▪ We anticipate calculating the number of subjects to compare two medians in case the primary
- 1637                   endpoint's distribution is not Gaussian. Indeed, let's consider a median difference of 0.3 in
- 1638                   international normalized ratio values instead of a mean difference. The sample size should be
- 1639                   25 patients with coagulopathy in each group, under the same assumptions of alpha (0.05) and
- 1640                   beta (20%) risk.

1641                   \*This intervention effect is only based on one thesis, and is not based on previous valid studies  
 1642                   because we could not identify such studies in the literature. We pragmatically chose the anticipated  

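### The stated 80% power is for 30 v 30 coagulopathic patients, but the primary test compares all mITT patients, and the plan gives no power for that test

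*Combined protocol and SAP*

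**What the plan says.** **Calculation.** Protocol section 8.2 states that "a sample size of 30 patients with coagulopathy in each group was adequate to detect a mean difference of 0.3 in INR values" at admission, "assuming a standard deviation of 0.4", with two-sided alpha 0.05 and 80% power. SAP section 16.5 says the same: "We calculated that a sample size of 30 patients with coagulopathy would be appropriate in each" group. Both divide 30 by an expected coagulopathy rate of 50% to get 60 per arm, allow 10% for missing consent, and round to 70 per arm (140 in total). A footnote in 16.5 ties the 50% to an INR threshold of 1.2.

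**Test.** Under Data Analysis for Primary Endpoint (section 8.1), INR at admission "will be compared across the two arms with the" Mann-Whitney U test. SAP section 16.7 agrees.

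**Population.** Section 8.7 defines the primary population as "mITT: taking into account all randomized patients except those for which the eligibility criteria were not met". The SAP's Analysis populations paragraph removes patients with an exclusion criterion. Neither removes patients without coagulopathy. Entry under section 4.1 depends on blood pressure or shock index only, and section 4.3 excludes only for a missing final sample or refusal. The per-protocol set additionally drops patients found not to be bleeding. None of the subgroups listed in 8.1 or 16.7 is defined by coagulopathy.

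**The concern.** Dividing by the coagulopathy rate makes sense only if the comparison is made among the 30 or so coagulopathic patients in each arm. The planned test instead pools them with an equal number of patients who are expected to arrive with an INR of 1.2 or below, and in whom a 0.3 fall is hard to picture. If those patients gain less than 0.3, the all-patient difference is smaller than the one used in the calculation.

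What is at stake is how the result is read. The SAP calls 0.3 the smallest clinically relevant difference. A non-significant mITT result would be set against a stated 80% power that was never worked out for that comparison.

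**Working it through.** **1. Inputs from the documents.** Difference 0.3 and SD 0.4 (both stated for coagulopathic patients), two-sided alpha 0.05, 80% power, 50% coagulopathic, 60 per arm before and 70 per arm after the loss allowance (8.2, 16.5). A 10% loss from 70 leaves 63 per arm.

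**2. The plan's own figure.**
- n per arm = 2 × (1.96 + 0.84)² × (0.4/0.3)² = 27.9; 28.9 by the t-test; about 30 after dividing the t-test figure by 0.955, the efficiency of the Mann-Whitney test for normal data.
- Power at 30 v 30 is 81.5% (t-test).
- 30/0.5 = 60 per arm; 60/0.9 = 66.7, rounded up to 70.

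The figures reproduce for the comparison they describe.

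**3. All-patient effect.** With half the patients coagulopathic, the all-patient mean difference is 0.5 × 0.3 + 0.5 × d, where d is the effect in the other half. The plan does not give d.
- d = 0 gives 0.15.
- d = 0.1 gives 0.20.
- d = 0.3 gives 0.30.

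**4. Power of the all-patient comparison** (two-sample t-test, standardised difference = difference/SD):

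| Difference | SD | 60 per arm | 63 per arm | 70 per arm |
|---|---|---|---|---|
| 0.15 (d = 0) | 0.4 | 53% | 55% | 60% |
| 0.15 (d = 0) | 0.5 | 37% | 39% | 42% |
| 0.20 (d = 0.1) | 0.4 | 78% | 80% | 84% |
| 0.30 (d = 0.3) | 0.4 | 98% | 99% | 99% |

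For d = 0 and SD 0.4, 80% power would need 2 × (1.96 + 0.84)² × (0.4/0.15)², about 112 per arm (113 by the t-test).

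**5. The SD is also open.** The 0.4 is stated within the coagulopathic calculation. In a 50:50 mixture the variance in one arm is 0.5 × 0.4² + 0.5 × s² + 0.25 × g², where s is the SD in the non-coagulopathic half and g is the gap between the two means in that arm. I averaged the control-arm variance (gap g) and the plasma-arm variance (gap g − 0.3). Assuming s from 0.1 to 0.4 and a control-arm g from 0 to 0.8 gives an overall SD of about 0.31 to 0.52. With d = 0, power is then about 35% to 75% at 60 per arm and 40% to 82% at 70 (normal approximation). So 0.4 may be too high or too low.

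**6. Mann-Whitney instead of the t-test.** For normal data the efficiency factor lowers the 53% at 60 per arm to about 52%. Simulated 50:50 mixtures with d = 0 gave about 31% to 48% at 60 per arm for several assumed normal and skewed shapes. They gave about 35% to 83% when coagulopathic values were skewed and floored near 1.0. These shapes are assumptions too; they show that the answer depends on the distribution.

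**The case against.** **The plan does not confine benefit to established coagulopathy.** Its hypothesis covers prevention as well as correction, so some effect in the other half is possible, and an effect of 0.1 there already brings power to about 80% at 63 per arm. This stands, and it limits any single figure. It does not rescue the stated 80%. The 50% is a rate at hospital arrival, so patients in whom plasma would prevent coagulopathy are already counted in the coagulopathic half. And if the full 0.3 were expected in everyone, doubling for prevalence would have been unnecessary.

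**Limits are disclosed.** SAP section 16.5 admits a fixed sample and a fall in power from 90% to 80%, and effects will be reported with 95% confidence intervals. Both soften the risk of misreading, but the 80% still belongs to a different comparison.

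A reader might also draw three stronger conclusions that the documents do not support:
- *That the true power is 53% on the plan's own inputs.* That figure needs zero effect in non-coagulopathic patients, an overall SD of 0.4 and 60 per arm. The plan states neither of the first two.
- *That the back-up figure of "approximately 25 coagulopathic patients per group, for a total of 120 patients" is an arithmetic error.* The steps that lead to 140 also give 25/0.5 = 50, 50/0.9 = 55.6, rounded up to 60 per arm, so 120. The derivation is unstated, but the figure follows.
- *That power should be recalculated at 30% prevalence* because section 1.3 says "a specific coagulopathy is found in about 30% of cases in injured patients". That describes injured patients generally. This trial selects on shock, and section 8.2 gives 50% for severely injured patients on arrival.

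**Conclusion.** The concern holds as a mismatch between the population in the power calculation and the population in the primary test. The arithmetic for 30 v 30 is sound. The 80% is not the power of the planned primary comparison, and the documents give no figure for that.

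If patients who would arrive at or below 1.2 gain nothing and the overall SD is 0.4, power is about 53% to 60% at 60 to 70 per arm. Over the same range of sizes it is about 37% to 42% at SD 0.5, and about 78% to 84% if the non-coagulopathic half gains 0.1 at SD 0.4. All of these rest on a 50% coagulopathy rate and a comparison of means. The effect in the other half and the all-patient SD are my assumptions, so the defensible statement is a range. A near-zero effect in patients at or below 1.2 is plausible, which makes the lower figures worth taking seriously.

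**What to change.** In protocol section 8.2 and SAP section 16.5:

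1. Say that the 80% refers only to a comparison of 30 v 30 coagulopathic patients.
2. State the effect assumed in non-coagulopathic patients, the resulting all-patient difference, and the all-patient SD.
3. Give the power of the planned mITT test as a range under those assumptions, at the numbers expected to be analysed.

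Optionally, pre-specify one supportive analysis in patients whose prehospital, pre-treatment INR exceeds 1.2, where it was measured. Selecting on arrival INR would not do, because that is the outcome. This subset may not reach 30 per arm: the 50% rate is for arrival, prehospital point-of-care testing was added by amendment in January 2017 (section 15), and the prehospital venous sample is taken only where possible (section 3.3.1).

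The cost is a change of wording and, if adopted, one more analysis. The stated power becomes less favourable. No extra patients are needed.
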